## Abstract

**Abstract:**

**Introduction:**

The ARFID InitiativE Sweden (ARIES) investigates the genetic and environmental factors contributing to avoidant/restrictive food intake disorder (ARFID) in children and adolescents aged 6–14 years. ARIES will establish a national biobank and research registry. It aims to provide data for immediate research and track ARFID outcomes and clarify genetic links between ARFID and other conditions and analyse the gut microbiome to guide nutrition interventions.

**Methods and analysis:**

The study will involve 1500 Swedish children and adolescents with ARFID and a control group of 500 Swedish children and adolescents without ARFID. Parents/guardians and their children will complete online questionnaires assessing ARFID and other eating disorder (ED) pathology, co-occurring conditions, quality of life and parental stress and ED pathology. All participants will provide a saliva sample for comprehensive genetic analyses. Additionally, a subset of participants will provide a stool sample to investigate the gut microbiome in ARFID.

**Ethics and dissemination:**

ARIES was approved by the Swedish Ethical Review Authority (Dnr 2023-04638). All participants will give assent and their parents will complete informed consent. Data will be made available by the authors on reasonable request. Findings will be published in scientific journals and shared with the public and stakeholders in accessible ways, for example, via social media.

STRENGTHS AND LIMITATIONS OF THIS STUDYThe ARFID InitiativE Sweden (ARIES) will be the largest epidemiological data collection of phenotype and genotype data in children and adolescents (6–14 years) with and without avoidant/restrictive food intake disorder (ARFID) to date.ARIES will establish a national research registry and biobank of childhood ARFID cases and controls containing comprehensive phenotype and genotype data enabling a wealth of research studies for many years to come.ARIES will be linked to Swedish population health and quality registers and, therefore, enable longitudinal follow-up to plot the course of ARFID and identify predictors of long-term outcome.The assessment of the ARFID phenotype relies on parent-reported questionnaires rather than clinical diagnoses, which allows for broader data collection in community settings where clinical diagnoses and structured diagnostic interviews may not always be available or feasible.Although the genome-wide association study (GWAS) sample size will be relatively small, integrating ARIES data with other ongoing collections globally will maximise statistical power for a coordinated GWAS meta-analysis, ensuring the most comprehensive and robust analysis to date and resulting in the largest ARFID GWAS conducted so far.

## Background

 The ARFID InitiativE Sweden (ARIES) study is designed to investigate genetic and environmental factors influencing avoidant/restrictive food intake disorder (ARFID) in children and adolescents between ages 6 and 14 years. ARIES is based on previous and ongoing research by the Eating Disorders Working Group of the Psychiatric Genomics Consortium (PGC-ED) including genome-wide association studies (GWASs) focused on the genetic basis of ARFID,^1^ anorexia nervosa (AN),^2^ bulimia nervosa (BN) and binge-eating disorder (BED).^3 4^ The overall aim is to explicate the genetic architecture of all EDs; their relationship to each other and to other psychiatric, neurodevelopmental, and somatic conditions and traits; and, ultimately, to facilitate a genetically informed nosology of EDs.

ARIES will contribute to this effort by providing detailed phenotype and genotype information of a large sample of children and adolescents with and without ARFID in Sweden. Using a subset of the sample, ARIES will provide information on the gut microbial environment in ARFID. ARIES will clarify within-disorder heterogeneity; identify genetic, environmental and microbial risk factors and correlates of the condition, and investigate the relation of ARFID to other EDs and psychiatric, neurodevelopmental and somatic conditions. The ultimate goal of this work is to provide important aetiological information to inform the development of effective interventions for ARFID.

ARFID is present in 1%–2% of the general population^5 6^ and was formally recognised in 2013.^7^ ARFID is a feeding and eating disorder characterised by an extremely restricted dietary quantity or variety resulting in significant weight loss, nutritional deficiencies, reliance on nutritional supplements and/or psychosocial impairment.^7^ In contrast to other EDs, ARFID occurs in approximately equal proportions of males and females,^6 8^ has an earlier age of onset^9^ and the restrictive eating is not primarily motivated by weight and shape concerns.^7^ ARFID is often accompanied by severe and sometimes life-threatening somatic and psychosocial comorbidities, leading to high social and financial burden for patients and their families.^10^,^14^ Despite the significant impairment, our knowledge on ARFID aetiology is limited. In part due to this insufficient understanding, evidence-based treatments are only starting to be developed^15^ and no specific treatment guidelines exist.^16^ A longer duration of untreated EDs other than ARFID has been found to decrease the likelihood of recovery.^17^ It is, therefore, likely that the lack of treatment options significantly contributes to the chronicity of ARFID.

ARFID is conceptualised as a single disorder; however, the Diagnostic and Statistical Manual of Mental Disorders fifth edition (DSM-5) describes three non-mutually exclusive presentations: (1) sensory-based food avoidance; (2) low appetite or interest in food and (3) fear of aversive consequences of eating. These symptom clusters overlap in a subset of individuals with ARFID (15%–51%).^818^,^20^ Comorbidities vary somewhat depending on the dominant presentation(s)^11 19^; for instance, sensory-based food avoidance has been shown to be more strongly related to neurodevelopmental conditions, low appetite or interest in food to mood disorders,^21^ and fear of aversive consequences to obsessive-compulsive disorder (OCD) and anxiety disorders.^11^

ARFID-related phenotypes such as appetite, food fussiness and food neophobia have been shown to be moderately to highly heritable.^22^,^25^ Our previous research using Swedish twin data further supports our aim of conducting a GWAS for ARFID: with a twin-based heritability of 70%–85%,^5^ ARFID is among the most heritable of EDs^26^ and of psychiatric conditions in general.^27^,^30^

In addition to identifying genetic risk factors for ARFID, ARIES is also exploring the role of the gut microbes (microbiota), along with their genes, collectively known as the gut microbiome. Disruption of the gut microbiota (dysbiosis) has been found both in children with severe malnutrition^31^ and in patients with AN^32^,^35^ and is commonly associated with cardiovascular diseases,^36^ cancer,^37^ neurological diseases^38^ and psychiatric conditions, such as anxiety and depression.^39^ Moreover, malnutrition in childhood has been found to be causally associated with immature gut microbiota.^31^ Nutrient intake and dietary variety during early childhood are essential for the establishment of rich and healthy gut microbiota,^40 41^ with the introduction of solid food being an important step towards the emergence of a complex and more adult-like gut microbiota.^40 42^ Prolonged restriction of food quantity and/or variety is likely to negatively impact the composition and function of the gut microbiota in ARFID. We, therefore, intend to study the association between ARFID-related eating habits and alterations in the gut microbiome.

### Aims

The overall aim of ARIES is to identify genetic, environmental and gut microbial factors associated with ARFID, with the goal of developing a comprehensive aetiological model. We will also characterise the phenotypic and genetic associations of ARFID with other EDs, as well as with psychiatric, neurodevelopmental, and somatic conditions and other relevant phenotypes (eg, metabolic, anthropometric). In this context, we will create a data repository comprising (1) parent-reported and self-reported phenotypic information on eating behaviours, co-occurring conditions, environmental exposures, health-related quality of life and healthcare utilisation and (2) a biorepository including saliva samples for genomic studies and stool samples for study of the gut microbiota. Both will be linked with Swedish health registers^43^,^45^ and the National Quality Register for Specialized Eating Disorder Treatment.^46^

#### Aim 1: characterise phenotypic features of ARFID

We will collect phenotypic information via online questionnaires and connect it with population health and quality registers to analyse demographics; symptom patterns; onset; disorder course; food intake; co-occurring psychiatric, neurodevelopmental and somatic conditions; environmental exposures; health-related quality of life and healthcare utilisation in people with ARFID. For most of these variables, we will also conduct analyses to compare ARFID cases with controls.

##### Hypotheses

Most participants with ARFID will show early childhood onset and a persistent course of illness. Furthermore, we expect participants with ARFID to report more co-occurring psychiatric, neurodevelopmental and somatic conditions than participants without ARFID. In terms of ARFID presentations, we expect to find sensory-based food avoidance to be related to autism, low appetite to depression and metabolic factors, and fear-based avoidance to anxiety and OCD.

### Aim 2: conduct a within-disorder ARFID GWAS

We will extract DNA from saliva samples provided by all participating children and adolescents. We will then (1) conduct a GWAS of the ARIES sample, (2) conduct a GWAS meta-analysis including other ARFID samples collected by the PGC-ED and (3) conduct a standard suite of genomic analyses.

#### Hypotheses

GWAS is a hypothesis-free method to identify genetic loci across the entire genome that are statistically associated with risk for a trait or a condition. We expect to identify genome-wide significant loci for ARFID.

### Aim 3: define the genetic relation of ARFID with other EDs

We will conduct a suite of analyses comparing ARFID to other EDs (AN, BN and BED) to examine their interrelations and investigate the overall genetic architecture of ARFID in comparison to other EDs.

#### Hypotheses

ARFID will share a core set of genetic factors with other EDs and be differentiated by disorder-specific genetic factors. ARFID will show the strongest genetic overlap with AN.

### Aim 4: define the genetic relation of ARFID with psychiatric, neurodevelopmental, somatic and other relevant phenotypes

We will conduct a suite of analyses comparing ARFID to psychiatric, neurodevelopmental, somatic and other relevant phenotypes to examine their interrelations and investigate the overall genetic architecture of ARFID in comparison to these phenotypes.

#### Hypotheses

Sensory-based food avoidance will be genetically related to autism, low appetite to depression and metabolic factors, and fear-based avoidance to anxiety and OCD. We also expect the genetic associations of ARFID with neurodevelopmental conditions and anxiety to be stronger than the genetic associations of ARFID with other EDs.

### Aim 5: explore the composition, diversity, maturity and function of the gut microbiome in participants with ARFID

We will collect and sequence stool samples from 100 cases and 100 controls to characterise the gut microbiomes and identify microbial genes and pathways associated with ARFID-related dietary, psychiatric, clinical and other relevant phenotypic factors.

#### Hypotheses

ARFID will be associated with reduced overall microbial diversity (similar to other EDs like AN), and immaturity of the gut microbiota. Specific microbial taxa, genes and pathways will be linked to ARFID pathology, dietary patterns and other ARFID-related phenotypes in participants with ARFID. For example, given that ARFID can involve selective eating habits, we expect to find changes in the levels of bacterial genera associated with diets characterised by specific macronutrient composition such as *Bacteroides* (associated with a diet high in animal proteins and fats) or *Prevotella* (associated with a diet high in carbohydrates and fibre) depending on specific dietary restrictions of individuals with ARFID.

## Methods

### Parent Advisory Council

A Parent Advisory Council (PAC) comprising eight parents/guardians of children and adolescents with ARFID will accompany our study to ensure maximum benefit on the community and support of parents/guardians of children with ARFID. Prior to the main study launch, the PAC completed a beta version of the entire study, including all questionnaires and saliva sampling and provided feedback on all study procedures.

### Participants

#### Objective

We will recruit 1500 children and adolescents aged 6–14 years with ARFID and 500 age-matched controls from Sweden to be included in the main study. 100 children and adolescents aged 6–14 years with ARFID, and 100 age-matched controls will also be selected and included in the microbiome substudy.

#### Recruitment

Study recruitment began in May 2024, and we anticipate closing recruitment in summer 2025. To ascertain cases, we developed and launched a campaign for information dissemination and recruitment using a variety of different methods, including social media, healthcare centres (eg, ED clinics, child and adolescent psychiatry, adult psychiatry and paediatric services), school healthcare and advocacy organisations for EDs and neurodevelopmental conditions. The Centre for Eating Disorders Innovation (CEDI) Social Media Committee assists in designing a campaign of informational material (print, audio and video) containing education about ARFID and invitations to participate in research. To ensure recruitment of a group of participants who represent ARFID distribution in the population, we include drawings of children and adolescents of different genders, ages, bodies and ancestries. To further increase reach, we recruit community members and influencers to promote ARIES. We focus the first part of our recruitment campaign to ascertain ARFID cases and the second part of our recruitment campaign to ascertain ARFID controls.

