#### Stool samples

Stool samples will be collected at home using the OMNIgene-GUT sample collection kit (OM-200, DNA Genotek) from participants included in the microbiome substudy. Parents will assist in conducting the stool collection and complete the Bristol Stool Scale.^50^ To guarantee safe transport and storage of the samples, the kits stabilise DNA at ambient temperature for 60 days. Prior to stool sampling, participants document their dietary intake in an online 24 hours food recall logbook.^51 52^

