#### DNA extraction and genotyping

Saliva samples will be stored at KI Biobank. We will use standard DNA extraction protocols and GWAS genotyping via the Illumina global screening array chip, or optimal methods available at the time of genotyping. Cases and controls will be randomised to plates.

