#### Data analysis

Research data will be pseudonymised for data analyses. We will follow predetermined statistical analysis plans for phenotype, genotype and gut microbiome data. All analyses will include age and sex/gender as covariates and be corrected for multiple testing.

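### Phased recruitment ties collection date to case status to an unknown degree; no balancing or adjustment for date is stated, and plate randomisation is stated for saliva only

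*Protocol article*

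**What the plan says.** All references are to the protocol article.

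- **Order and window (Recruitment).** The first part of the campaign has its focus on cases; the authors then focus "the second part of our recruitment campaign to ascertain ARFID controls". On timing: "Study recruitment began in May 2024, and we anticipate closing recruitment in summer 2025". No date is given for the switch between the two parts.
- **Timing of data (Procedure, Stool samples).** Registration and screening come first. Eligible families then complete the further questionnaires and are mailed the saliva kit and, in the substudy, the stool kit. The food recall is completed before stool sampling.
- **Groups (Objective).** The main study has "1500 children and adolescents aged 6–14 years with ARFID and 500 age-matched controls from Sweden". For stool, "100 children and adolescents aged 6–14 years with ARFID, and 100 age-matched controls will also be selected and included in the microbiome substudy". Age is the only matching variable named.
- **Batching.** The section DNA extraction and genotyping, which deals with saliva, says: "Cases and controls will be randomised to plates". The corresponding section on microbial DNA extraction and sequencing describes biobank storage, extraction and sequencing but no such step.
- **Stool kit (Stool samples).** One kit type serves all substudy participants, and "the kits stabilise DNA at ambient temperature for 60 days".
- **Covariates (Data analysis).** "All analyses will include age and sex/gender as covariates". The same section refers to predetermined analysis plans, which are not shown.

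**The concern.** If cases tend to supply data earlier than controls, anything that drifts between the two parts of the campaign is partly mixed with case status. Candidates are diet over the year, time that stool spends in storage, and answers about current symptoms, anxiety or quality of life.

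The analyses exposed are those of things that can change within months:

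- Shannon index, beta-diversity and differential abundance at 100 v 100.
- The microbiota-for-age Z-scores. Controls supply the reference here, so a period shift in the controls would carry into every case's score.
- The 24-hour food recall.
- Case-control comparisons of current-state questionnaires in the main study.

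The recruitment order is a design decision made in this document. An analysis plan can add a date covariate, but it cannot create overlap in time that recruitment did not produce.

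**Working it through.** The plan gives no figure on this point, so there is none to reproduce. The check has two parts.

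**1. What the text establishes**

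- Phased focus, with data collection after registration, makes collection date associated with case status.
- Age matching and the age and sex/gender covariates do not remove an association with date.
- The stated plate randomisation concerns saliva DNA. Germline genotype does not vary with season, so the GWAS is not at issue.

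**2. Illustration of size**

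Inputs from the article: 100 v 100 (substudy) and 1500 v 500 (main study). Assumed, because the article gives neither: the period shift d in SD units, and the shares of cases (a) and controls (b) in the first part. No true case-control difference is assumed, and one outcome is tested two-sided at 5% without multiplicity correction.

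- Bias = (a − b) × d
- SE = √(1/n₁ + 1/n₂), which is √(2/100) = 0.141 SD for 100 v 100 and √(1/1500 + 1/500) = 0.052 SD for 1500 v 500
- False-positive rate = 1 − Φ(1.96 − bias/SE) + Φ(−1.96 − bias/SE)

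For 100 v 100:

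| Shift d | a − b | Bias (SD) | False-positive rate |
|---|---|---|---|
| any | 0 (concurrent collection) | 0 | 5% |
| 0.2 | 0.4 | 0.08 | 8.7% |
| 0.2 | 0.6 (80/20 v 20/80) | 0.12 | 13.6% |
| 0.3 | 0.6 (80/20 v 20/80) | 0.18 | 24.7% |
| 0.3 | 1.0 (full separation) | 0.30 | 56.4% |

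Worked line: 0.18/0.141 = 1.27, and 1 − Φ(1.96 − 1.27) + Φ(−1.96 − 1.27) ≈ 0.247.

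The larger sample is more sensitive to the same bias. At 1500 v 500 with d = 0.2 and a − b = 0.6, the rate is 64.2%.

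**Cost of adjusting for period instead.** With equal groups and splits symmetric about one half, the squared correlation of case status with period is r² = (a − b)², and the variance of the case-control contrast is multiplied by 1/(1 − r²):

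- 70/30 v 30/70: 1/(1 − 0.16) = 1.19
- 80/20 v 20/80: 1/(1 − 0.36) = 1.56, equivalent to 100/1.56 ≈ 64 per group
- 90/10 v 10/90: 1/(1 − 0.64) = 2.78, equivalent to 100/2.78 ≈ 36 per group
- No overlap: not estimable

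**The case against.** The strongest reply is that the article describes a campaign emphasis, that a condensed article need not set out plate layouts or every covariate, and that the figures above are invented inputs. Much of that stands, and several stronger readings that a reader might infer are not supported.

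- **That the groups are recruited in separate periods.** The word used is focus. Nothing says enrolment of either group closes in either part, and status is set by screening after registration. Full separation is only a limiting case.
- **That season is wholly confounded with case status.** The window exceeds a year, so both parts may include late spring or summer months.
- **That case and control stool is handled differently.** Kit and biobank are the same for all. The 60-day figure is a stability limit for every sample, not evidence of a difference. The article does not say when stool kits go out relative to the campaign phases, or that samples are processed in order of arrival. If all stool is stored and then extracted together in mixed order, processing batch is not confounded, although collection date still could be.
- **That stool will not be randomised, or date not adjusted for.** The covariate sentence can be read as a minimum, and the analysis plans are not shown. Absence from the article is not an error.
- **That 25% or 56% is the expected error rate.** Both rest on assumed shifts and splits and on one uncorrected test. The plan says it corrects for multiple testing.

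What the reply does not remove is the phasing itself. It is stated, nothing stated offsets it, and if overlap proves poor a later analysis plan can repair it only in part.

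**Conclusion.** The point holds as a modest, inexpensive design improvement. By the stated recruitment order, collection date is associated with case status to an unknown degree, and the article states no balancing or adjustment for it. It applies to the microbiome comparison, including the control-referenced Z-scores, the food recall and current-state questionnaires, and not to the GWAS.

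Its size cannot be derived from the document. The scenarios shown for 100 v 100 run from the nominal 5% under concurrent collection to 56% in the limiting case. They show that the issue can matter, not that it does.

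**What to change.** 1. For the stool substudy, send kits to the selected cases and controls in the same calendar months. Where still possible, keep enrolment of both groups open together for the rest of the campaign.
2. State that stool samples are randomised to extraction plates and sequencing runs, balanced by case status, as is already stated for saliva plates.
3. Add collection month or season as a covariate in the microbiome, diet and current-state questionnaire comparisons, at least as a sensitivity analysis, and report the distribution of collection dates by group.

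The cost is some scheduling effort and a randomised plate layout; kit returns and online questionnaires should already carry dates. Date adjustment also costs precision, by the variance factors shown above, and it fails if there is no overlap. Step 1 therefore matters more than step 3.

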### Procedure

Parents/guardians of children and adolescents with ARFID who are interested in participation will be referred to the study website (www.ariesstudy.se) that provides detailed study information and contact details in case of questions (‘parents/guardians’ will henceforth be referred to as ‘parents’ for readability). To be eligible for participation, all individuals must have a valid Swedish personal number (a unique national identification number), which is required for both providing consent and linking to the Swedish National Health Registers. Study information is provided in three versions: for children (6–11 years), for adolescents (12–14 years), and for parents. If interested in participation, parents can register their child and provide online informed consent on the study’s website. Parents will complete online screening questionnaires covering ARFID and other disordered eating cognitions and behaviours including the Pica, ARFID and Rumination Disorder Interview-ARFID Questionnaire (PARDI-AR-Q),^47^ the Nine Item ARFID Screen (NIAS)^48^ and the parent version of the Eating Disorder Examination Questionnaire (PEDE-Q).^49^

The online screening questionnaires will be used to create a diagnostic algorithm for DSM-5 ARFID and determine eligibility and case status of the child. If the child is eligible for the study by parent-report, parents are instructed to complete additional questionnaires (some are mandatory, some are optional; online supplemental table S1). Additionally, we implemented optional self-report questionnaires for adolescents. A saliva sample collection kit including return packaging is mailed to the parent’s address with directions for saliva collection from the child. Those participating in the microbiome substudy will also receive a stool collection kit. Participation in the main study will be complete as soon as the kits are received by Karolinska Institutet (KI) Biobank and all mandatory questionnaires are completed. All participants receive two cinema tickets as soon as participation in the main study is complete. We do not provide participants in the microbiome substudy with additional reimbursement.

